#### Eligibility Criteria

To be eligible, potential participants must be females aged 15 to 24, currently in a sexual relationship with a male partner for at least 1 month, and vulnerable to HIV per a modified version of the DREAMS eligibility screening tool. To reflect the population most likely to participate in this intervention in a programmatic setting, they must be either taking PrEP or interested in taking PrEP (ie, she thinks that she would benefit from PrEP but is not currently taking it). In addition, they must be residents of the applicable study ward; willing and able to attend support clubs; willing and able to provide adequate contact information; fluent in English, Dholuo, or Kiswahili; and able and willing to provide informed consent (or assent and parental consent for nonmature minor participants aged 15 to 17). Potential participants are excluded if they are living with HIV (by self-report); planning any long-term travel or relocation in the next 12 months; or have any condition that the site PI or designee determines would preclude participation.

Individuals who do not meet the criteria for participation in this trial (ie, screen failure) because of criteria that are likely to change over time may be rescreened. Examples include not being resident of the ward or not being interested in taking PrEP.

#### Recruitment and Screening

Recruitment occurs simultaneously in each pair of wards before moving on to the next pair and focuses on the catchment areas of 2 to 4 health facilities in each ward. Before recruitment, community mapping is conducted to identify key stakeholders, referral resources, locations where adolescent girls and young women gather, and locations where men gather. Recruitment takes place at venues identified through community mapping, including health facilities, schools, churches, DREAMS Safe Spaces, youth groups, and community markets. To ensure that the study findings are generalizable to adolescent girls and young women across the 15- to 24-year age range, we aim to enroll at least 25% of the study participants from the 15- to 19-year age group who have lower rates of PrEP use but have similar HIV incidence to the 20- to 24-year age group [47,48]. Attendees interested in the study are invited to meet with the research assistant after the recruitment meeting to discuss questions, obtain additional information, and schedule an appointment for informed consent, eligibility screening, and, if eligible, for enrollment.

#### Retention

Once a participant is enrolled in the study, the study team makes every reasonable effort to retain her to minimize bias associated with loss to follow-up. To ensure high retention, IRDO tracks retention rates and follows standard study operating procedures detailing strategies, such as clear explanation of the visit schedule at all visits, collection of detailed locator information with multiple means to contact participants, appropriate and timely visit reminders, offering weekend hours for study visits, and conducting immediate follow-up on missed visits through phone, home or other off-site visits.

#### Intervention and Control Conditions

##### Intervention Design

Tu’Washindi was developed by our team using a participatory process with adolescent girls and young women and service providers in Siaya County to ensure that it was responsive to adolescent girls and young women’s stated needs for PrEP support in the context of their relationships [40]. The intervention components are informed by social cognitive theory [49] in combination with a socioecologic framework for PrEP introduction [50] to address factors at the individual, partnership, and community levels that influence adolescent girls and young women’s response to IPV and their PrEP use (Figure 2 [50,51]).

Social cognitive theory informs support club activities to enhance individual-level behavioral capability (eg, knowledge and skills to use PrEP and IPV safety planning), improve outcomes expectations (eg, that PrEP use will prevent HIV without threats to safety or relationship security), and increase self-efficacy to use PrEP safely and consistently. At the partnership level, support clubs also aim to develop skills for healthy communication and PrEP disclosure. Drama activities are integrated into each session to allow participants to practice these skills and build self-efficacy. Adolescent girls and young women follow suggested storylines from the intervention manual, developed by youth in the formative phase [40], to create and enact plays about overcoming partner-related barriers to PrEP use, including one to be performed at the Buddy Days. Buddy Days also work at this level to facilitate disclosure and build male partner support for PrEP use by engaging couples in discussions about PrEP, healthy relationships, and promoting HIV prevention as part of family well-being. To increase men’s receptiveness to information provided at the Buddy Days or from their female partners, community sensitization events deliver accurate information about PrEP (eg, safety, effectiveness, and eligibility), discuss common myths and misperceptions, and encourage men to support their partners’ PrEP use [53]. At the community level, the community sensitization activities aim to increase PrEP knowledge, reduce PrEP stigma, and reduce the acceptability or normalization of IPV as a response to adolescent girls and young women’s PrEP use. Support clubs aim to increase social assets, including peer support for PrEP use and access to IPV resources in the community. Table 1 illustrates the intervention’s alignment with the conceptual framework.

**Figure 2 figure2:**
[figure not shown]
The conceptual framework; adapted from Pettifor et al [51] and Mathur et al [50]. IPV: intimate partner violence; PrEP: preexposure prophylaxis.

**Table 1 table1:** Mapping of intervention components to conceptual framework.

Level and domain			Community sensitization		Buddy Days		Support clubs
**Individual**							
	Behavioral capability					✓	
	Outcomes expectations			✓		✓	
	Self-efficacy					✓	
**Partnership**							
	Healthy communication			✓		✓	
	Reduce intimate partner violence acceptability	✓		✓		✓	
	Disclosure of preexposure prophylaxis use			✓		✓	
	Partner support or acceptance	✓		✓			
**Community**							
	Preexposure prophylaxis knowledge	✓		✓			
	Stigma	✓					
	Social assets					✓	

##### Intervention Delivery

Before delivery, the intervention manual and training tools were updated to reflect lessons learned during the pilot and the change to implementation outside of DREAMS. Because age restrictions on PrEP in DREAMS did not permit us to pilot the intervention with adolescent girls aged 15 to 17 years, we pretested the activities with 12 to 15 adolescent girls in this age range over a 1-month period to obtain feedback on comprehension and relevance of the content and how best to support participation.

Delivery takes place in 4 phases, with activities occurring concurrently in 2 wards during phase 1 and in 3 wards during phases 2 to 4. In each ward, the intervention is conducted over a 6-month period with intervention implementation beginning about 1 week after enrollment concludes. Each new phase of the intervention commences immediately after the activities in the previous phase are concluded. This phased approach minimizes staff burden and allows for close monitoring of implementation to identify and correct problems early on.

The intervention activities include sensitization of MoH clinics, intervention staffing and training, community sensitization sessions, Buddy Days, support clubs, and monitoring and quality assurance.

For sensitization of MoH clinics, before study initiation in each intervention ward, we collaborate with the facility in-charges from each of the 2 to 4 health facilities selected for study recruitment to identify PrEP delivery staff and schedule a half to one day training to introduce the study and discuss relationship-related challenges to PrEP use, with the goal of ensuring that the counseling support offered at the clinics complements the messages provided through the intervention. We also review PrEP adherence and couples’ counseling and disclosure approaches to more comprehensively address adherence challenges commonly experienced by adolescent girls and young women.

Intervention staffing and training within each ward is delivered by a set of 2 to 4 mentors (ie, women slightly older than the participants who have completed at least some secondary education and are rooted in their communities), an experienced male community organizer, and clinicians and counselors with experience in PrEP provision to adolescent girls and young women (hereafter “intervention providers”). Staff supervisors train each cadre over 1 to 3 days to review the intervention manual and to practice the required activities.

Community sensitization sessions are conducted by the community organizer approximately weekly over the first 3 months of the intervention period, lasting about 60 minutes to 90 minutes each. Sessions occur in places where adolescent girls and young women’s male partners are known to gather [54]. Content focuses on PrEP information and dispelling myths and rumors. When time allows, additional content on healthy relationship communication is also included. Clinicians may attend larger sessions to support the organizer.

Buddy Days take place around month 3 of the intervention period, with about 2 to 3 events per ward to maximize participation. The sessions are cofacilitated by the community organizer and clinician and include provision of information about PrEP; facilitated discussion of reasons to support adolescent girls and young women’s PrEP use, healthy relationship communication, and acceptability of IPV; and an interactive drama, designed and performed by volunteer Tu’Washindi participants based on story guides in the intervention manual, to illustrate real-world partner-related challenges to PrEP use. The cofacilitators foster audience engagement both during and after the performance by soliciting reflections on the drama, discussions of alternate storylines, and experiences from audience members [55]. To encourage and destigmatize participation, Buddy Days are open to all community members and offer health services, such as HIV testing services and screening for hypertension and diabetes. In addition, all adolescent girls and young women and their partners who attend the Buddy Days together as a couple receive a small basket of foodstuffs worth about US $5 as an incentive.

Support clubs meet for approximately eight 2-hour sessions over the 6-month intervention period, facilitated by the mentor or by 1 or more participants with mentor support. About 3 to 4 support clubs are offered at varying times and locations to maximize convenience and maintain a small enough number of attendees (18-24) to build community and trust. The support clubs aim to be youth-friendly and nonjudgmental, with an emphasis on ground rules and confidentiality, and support for PrEP uptake and adherence are integrated throughout. Each interactive, participatory session follows the same basic format: a check-in and activity to build community; recap of the previous session; a new topic related to PrEP and relationships, led by the mentor, clinician, or counselor (Table 2); drama activities; and a closing activity to reflect on lessons learned and build confidence and support.

**Table 2 table2:** Sample support club topics and coleaders.

Session and topic	Leaders
Session 1: PrEP^a^ information	Mentor and clinician
Session 2: disclosure	Mentor and counselor
Session 3: undisclosed PrEP use	Mentor and clinician
Session 4: healthy relationships	Mentor and counselor
Session 5: IPV^b^ and PrEP use	Mentor and counselor
Session 6: open session^c^	Mentor
Session 7: open session^c^	Mentor
Session 8: future goals and closing ceremony	Mentor

^a^PrEP: preexposure prophylaxis.

^b^IPV: intimate partner violence.

^c^Participants’ choice of topics.

Monitoring and quality assurance involves closely monitoring intervention delivery for quality and fidelity. Staff supervisors will observe at least 15% of community sensitization activities, 100% of Buddy Days, and at least 20% of support clubs using activity-specific observation forms to document assessments of fidelity (ie, adherence to the intervention manual), quality of facilitation (eg, facilitator maintains focus and nonjudgmental delivery), participant engagement, and any factors that may have affected implementation. Intervention staff receive feedback and coaching after each observed session. Findings will inform staff retraining and implementation refinement for subsequent phases. For example, training of intervention providers may be bolstered if gaps are identified.

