## Methods

### Design

This study has a 2-arm parallel cRCT design (Figure 1). We have randomized 22 administrative wards in a 1:1 ratio and aim to enroll about 72 adolescent girls and young women from each (total N=about 1584) to receive either the Tu’Washindi intervention plus usual HIV prevention services, or usual HIV prevention services alone. Because of the urgent need for interventions to support PrEP use among adolescent girls and young women in a real-world context, the intervention is delivered outside of DREAMS to evaluate its impact on adolescent girls and young women accessing PrEP from Ministry of Health (MoH) facilities. This pragmatic study design enables us to determine effectiveness of the intervention when layered onto ongoing county-wide HIV prevention programming [44]. After informed consent and baseline data collection, the Tu’Washindi intervention is implemented in each intervention cluster while the control cluster continues with usual HIV prevention services. The duration of study participation is 12 months, with data collection visits at intervention midline (study month 3), intervention endline (study month 6), and at 6 months postintervention (study month 12). A prospective process evaluation is being conducted to characterize intervention implementation, explore theorized mechanisms of change, and capture contextual factors influencing study outcomes. The protocol was written following the 2013 SPIRIT (Standard Protocol Items: Recommendations for Interventional Trials) guidelines (Multimedia Appendix 1).

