**Exploratory outcomes (subcomponents or alternate measures of primary and secondary outcomes)**		
	PrEP uptake	Percentage of participants initiating PrEP *among those not on PrEP at baseline*, self-reported and validated by Ministry of Health records.
	PrEP execution	Percentage of participants with TFVdp levels indicating consistent use *among those reporting current PrEP use.*
	PrEP persistence	Percentage of participants with any detectable TFVdp *among those who ever initiated PrEP.* Participants who self-report discontinuation will be categorized as having undetectable TFVdp levels.
	Recent PrEP use (biomarker)	Percentage of all study participants with biomarker FTCtp^e^ levels indicating consistent PrEP use (≥4 doses per week) for the past 2 wk. Collected at months 6 and 12 only.
	IPV type	Percentage of participants reporting each IPV type (physical, sexual, emotional, and economic) since the last visit, per WHO VAWI [70].

^a^PrEP; preexposure prophylaxis.

^b^TFVdp: tenofovir diphosphate.

^c^IPV: intimate partner violence.

^d^WHO VAWI: World Health Organization’s Violence Against Women instrument.

^e^FTCtp: emtricitabine triphosphate.

The secondary outcomes of the study will be the proportion of participants reporting any IPV and severe IPV (Table 4) between enrollment and month 6, and between month 6 and month 12, and the difference in IPV intensity scores at months 6 and 12. The aim 2 hypothesis is that the proportion of participants reporting any IPV and severe IPV and IPV severity scores will all be *lower* at both time points in the intervention arm versus control arm.

In exploratory analyses, we will first explore effect modification by age (15-19 vs 20-24) and DREAMS participation (current, former, or never) for the primary and secondary outcomes. Second, we will break down the primary outcome into steps along the continuum (PrEP uptake, execution, and persistence) and IPV outcomes by type—physical, sexual, emotional, and economic—to understand where the intervention had its strongest effects. Third, we will compare the proportion of participants per arm with emtricitabine triphosphate (FTCtp) levels indicating consistent PrEP adherence over the past 2 weeks. Comparing TFVdp and FTCtp levels will yield insights on adherence patterns over both a long and short window of time before collection. We will also analyze the alignment of adherence measures with HIV risk perception and behavior to better understand adherence patterns.

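### Training of PrEP staff at the recruitment clinics, listed as an intervention activity, appears to precede study initiation in intervention wards, so baseline there may not be pre-intervention for the analyses that condition on it

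*Protocol article*

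**What the plan says.** Intervention Delivery opens its list of activities this way: "The intervention activities include sensitization of MoH clinics, intervention staffing and training, community sensitization sessions, Buddy Days, support clubs". On the first item it says: "For sensitization of MoH clinics, before study initiation in each intervention ward, we collaborate with the facility in-charges". The facilities concerned are the "2 to 4 health facilities selected for study recruitment to identify PrEP delivery staff and schedule a half to one day training". The content goes beyond logistics: the training introduces the study, discusses relationship-related obstacles to PrEP, and then "We also review PrEP adherence and couples’ counseling and disclosure approaches to more comprehensively address adherence challenges". The stated goal is that clinic counseling should support the intervention's messages. No counterpart is described for control wards.

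Two statements put the start of the intervention later. Design says: "After informed consent and baseline data collection, the Tu’Washindi intervention is implemented in each intervention cluster". Intervention Delivery itself has implementation begin roughly a week after enrollment in the ward closes.

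The trained clinics lie on the recruitment pathway. Under Recruitment and Screening: "Recruitment takes place at venues identified through community mapping, including health facilities". Under Usual Care Services, participants who want PrEP can obtain it from MoH facilities.

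Three analyses use baseline:
- Table 4 defines the exploratory uptake outcome as "Percentage of participants initiating PrEP", restricted to women not on PrEP at baseline.
- Quantitative Data, under the process evaluation, regresses each mechanism on arm while controlling for its baseline level.
- Analysis Approach allows exploratory models that adjust for baseline characteristics found to be unbalanced.

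**The concern.** A baseline measured after part of the intervention has begun, in one arm only, is no longer a neutral reference. Women seen by newly trained staff could start PrEP, disclose its use or gain confidence before they answer the enrollment questionnaire.

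For uptake, those women leave the intervention-arm denominator before counting starts, and they are the ones readiest to initiate. For the mechanism models, adjusting for a baseline score that the training has already moved removes part of the effect being estimated. This matters because the protocol would use those models, after a null result, to judge whether the intervention failed to move the mechanism or whether the mechanism failed to move the outcome. For the exploratory adjusted models, an imbalance created by the training could itself trigger the adjustment that removes part of the effect.

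**Working it through.** **1. Timing.** Three statements are set side by side: clinic training is an intervention activity; the work on it is tied to the period before study initiation; the intervention starts after baseline and after enrollment. Taken literally, they cannot all hold. The early phrase attaches to working with facility heads to identify staff and schedule the training, and no training date is given. That the training also introduces the study suggests an early date but does not establish one.

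**2. Which analyses are exposed.**

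| Analysis | Uses baseline? | Exposed? |
|---|---|---|
| Primary, effective PrEP use | No: all participants; arm, strata, ward effect | Not by conditioning on baseline |
| Secondary, IPV | No baseline covariate | Not by conditioning on baseline |
| Exploratory uptake | Denominator set by baseline PrEP status | Yes |
| Mechanism models | Baseline level as covariate | Yes |
| Exploratory adjusted models | Unbalanced baseline characteristics | Yes |

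**3. Uptake.** The plan gives no figure to reproduce, so every rate here is assumed. Let *u* be true total uptake among women not on PrEP before the training, and *f* the share of them who start between training and baseline, all of whom would have started by month 6 anyway. Observed uptake = (*u* − *f*)/(1 − *f*). With *u* = 45% in intervention wards, 30% in control wards and 20% already on PrEP before the training, the true difference is 15 points.

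| *f* | On PrEP at baseline, intervention (0.20 + 0.80*f*) | Observed uptake, intervention | Observed difference |
|---|---|---|---|
| 0 | 20% | 45.0% | 15.0 points |
| 2% | 21.6% | 0.43/0.98 = 43.9% | 13.9 points |
| 5% | 24% | 0.40/0.95 = 42.1% | 12.1 points |
| 10% | 28% | 0.35/0.90 = 38.9% | 8.9 points |
| 15% | 32% | 0.30/0.85 = 35.3% | 5.3 points |

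A second set of assumed numbers, with no true difference between arms, moves the same way. If 32 of 80 non-users would initiate (40%) and 2, 5 or 10 of them start before baseline, measured intervention uptake is 30/78 = 38.5%, 27/75 = 36.0% or 22/70 = 31.4%.

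**4. Mechanism models.** In a linear model with baseline slope *b*, the adjusted arm effect equals the difference in follow-up means minus *b* times the difference in baseline means. If the training raised the intervention baseline by *d*, then *b* × *d* of the effect is subtracted. The document supplies neither quantity. A model without the baseline term does not subtract it.

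**5. Primary outcome.** The only remaining route is composition: trained clinics might channel more current users into the sample. Assume effective use of 40% in baseline users and 15% in others. An excess of 2.5, 5 or 10 points in the share of users then shifts the arm difference by that excess × 0.25, which is 0.6, 1.25 or 2.5 points, against the 15-point design difference. Nothing in the document shows such channelling.

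**The case against.** The strongest reply is that the intervention proper has three components (support clubs, Buddy Days, community sensitization), and that preparing providers naturally precedes delivery. The list containing clinic sensitization also holds staffing and quality assurance. On that reading, the statements about starting after enrollment refer to participant-facing delivery, and the early phrase covers only scheduling. This is a fair reading and weakens the contradiction. It does not remove it: the clinic work is named as an intervention activity, carries counseling content and has no stated date.

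Other parts of the reply also stand. That control clinics had nothing comparable is an inference from silence in a condensed article. The effect of a half-day to one-day staff training on PrEP starts in an unknown interval may be small: the Introduction cites 4% initiation in a western Kenya family planning study, recruitment also uses schools, churches and markets, and PrEP is available at more than 100 facilities.

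A reader might infer that the contrasts are in fact distorted, or that the primary result is biased. The document supports neither. It shows a risk that depends on an unstated date. A woman who moves from interested in PrEP to taking it is eligible either way, so early starting alone does not change who is enrolled, and the primary model does not condition on baseline.

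**Conclusion.** The point holds as a timing inconsistency with a limited analytic consequence. If the training precedes enrollment, baseline in intervention wards can be post-exposure for three analyses: exploratory uptake, the mechanism models and the exploratory covariate-adjusted models. For uptake the likely direction is toward the null when early starters would have initiated anyway. Selective recruitment through trained clinics could push it either way. The illustrations run from about 1 point lost (2% early starters) to about 10 points lost (15%) out of a true 15, but every rate is assumed, and neither size nor direction can be settled from the document. The primary intent-to-treat contrast is at most slightly affected.

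**What to change.** - Reconcile Design and Intervention Delivery by stating when the clinic training occurs relative to enrollment and baseline, and what clinics in control wards receive.
- Where feasible in wards not yet started, complete enrollment and baseline before the counseling content is delivered, with only a neutral study introduction beforehand. The reach is small: by December 2024 enrollment was complete in 16 of 22 wards, leaving 6, or 3 intervention wards given paired recruitment. With 12 months of follow-up and data collection ending in May 2026, the last enrollments would fall around May 2025.
- In all wards, record the training date, using the paired intervention ward's date for each control ward. Run a sensitivity analysis of uptake that sets the denominator by PrEP status before that date and counts starts between that date and enrollment as initiations. The enrollment PrEP history and the MoH records already used for validation are the sources; check that they give start dates.
- Report each mechanism model without baseline adjustment beside the adjusted one, and read the two together.

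The cost is slightly later training in any re-timed ward, a small difference in delivery between earlier and later wards, and one or two extra analyses. No new participant procedures are needed.
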